## Abstract

**Background:**

Optimal application of the recently updated World Health Organization (WHO) guidelines for exercise in advanced age necessitates an accurate adjustment for the age-related increasing variability in biological age and fitness levels, alongside detailed recommendations across a range of motor fitness components, including balance, strength, and flexibility. We previously developed and validated a novel tool, designed to both remotely assess these fitness components, and subsequently deliver a personalized exercise program via smartphone.
We describe the design of a prospective randomized control trial, comparing the effectiveness of the remotely delivered personalized multicomponent exercise program to either WHO exercise guidelines or no intervention.

**Methods:**

Participants (*n* = 300) are community dwelling, healthy, functionally independent, cognitively intact volunteers aged ≥65 at low risk for serious fall injuries, assigned using permuted block randomization (age/gender) to intervention, active-control, or control group. The intervention is an 8-week program including individually tailored exercises for upper/lower body, flexibility, strength, and balance (dynamic, static, vestibular); active-controls receive exercising counselling according to WHO guidelines; controls receive no guidance. Primary outcome is participant fitness level, operationalized as 42 digital markers generated from 10 motor fitness measures (balance, strength, flexibility); measured at baseline, mid-trial (4-weeks), trial-end (8-weeks), and follow-up (12-weeks). Target sample size is 300 participants to provide 99% power for moderate and high effect sizes (Cohen’s f = 0.25, 0.40 respectively).

**Discussion:**

The study will help understand the value of individualized motor fitness assessment used to generate personalized multicomponent exercise programs, delivered remotely among older adults.

**Trial registration:**

ClinicalTrials.gov Identifier: NCT04181983

**Supplementary Information:**

The online version contains supplementary material available at 10.1186/s12877-021-02559-2.

## Background

In 2020 the World Health Organization (WHO) published the new evidence-based guidelines for exercise among adults aged ≥65, comprising 150–300 min of moderate-intensity, or 75–150 min of vigorous-intensity physical activity, per week, combined with ≥three times a week of multicomponent physical activity that emphasizes functional balance and strength training at moderate or greater intensity [1]. In order to optimize the benefits of these exercise guidelines across the wide and varied target population of older people, two major challenges must be addressed.

Firstly, the widening gap between chronological and biological age, which typifies advancing age, raises into question the benefits of general guidelines for a certain chronological age. The growing variability between biological and chronological age is well recognized in aging research, and highlights the dangers and inexactitude involved in chronological age determined standards and reference ranges [2]. For example, modeling the relationship between numerus biological markers and an individual’s chronological age raises questions about the nature of aging [2], as witnessed by the differential trajectories of age-related decline experienced by individuals with the same chronological age. Thus biological age should be assessed distinctly from chronological age [3].

Furthermore, the gap between biological and chronological age widens with advancing age across a multitude of molecular and physiological systems [3] as well as performance measures [4]. This gap raises the question whether “one-size-fits-all” strategy in exercise recommendations for older adults is effective. This question is even more relevant in light of the rapid growth of the field of precision personalized medicine, enabled by artificial intelligence (AI). According to Johnson et al., [5], current research which integrates AI into precision medicine, is driving towards a highly personalized medical diagnostic and therapeutic information. While personalized medicine refers primarily to diagnostics and therapeutics for disease treatment, it also emphasizes the prevention and risks prediction aspects as well as the health or wellbeing of every person [6, 7].

A second challenge is the imprecise information provided in the general guidelines regarding fitness components related to the musculoskeletal (movement) system as opposed to the cardiovascular system. While the guidelines for aerobic exercise (aimed at enhancing the cardiovascular system) are specific in terms of optimal dose, intensity or duration, the guidelines remain vague for strength, balance and flexibility (movement system). One reason may be attributed to difficulties in accurate measurement, required for an accurate assessment of the level of fitness in skeletal muscle performance or postural stability in non-laboratory settings. Another reason is the priority given by researchers to energy expenditure, mainly aerobic exercise, in promoting health (e.g. [8–10]). The promotion of aerobic activity is often at the expense of under emphasizing the fitness of the motor system, including balance, strength and flexibility- all of which are critically important in preventing falls, improving the musculo-skeletal performance, and range of motion ([11–13] respectively) in advanced age. It is therefore not surprising that technological innovations to promote and monitor physical activity on an individual basis, such as fitness trackers and mobile phone applications, which usually measure accumulation of repetitive movements, such as the number of steps or movements of legs or arms, are designed primarily to provide information on energy expenditure equivalent to cardiovascular (aerobic) exercise (e.g. [14–16]). Importantly, these technological innovations are typically designed to attract mainly young adults.

Recognizing the importance of addressing these challenges in order to promote optimal exercise among people over aged ≥65, the Israeli Ministry of Innovation, Science and Technology awarded a grant to develop a novel approach towards a personalized exercise program based on individualized assessment of multiple movement components in healthy older adults. Obviating the need for detailed assessment either in a laboratory or by trained professionals, we proposed to develop a novel tool able to remotely assess balance, flexibility, and strength using smartphone sensors (i.e. accelerometer and gyroscope). Based upon data from this multicomponent assessment, the study tool was then designed to subsequently deliver personalized exercise programs tailored to address these movement components via the smartphone.

We recently described the design, development, validation, and results from the pilot study [17], which confirm the proof of concept and feasibility of the study tool. Briefly, an interdisciplinary panel of experts chose the motor components to be included in the remote fitness assessment, and the standard movement performance tests to best assess them. These were incorporated into a smartphone application, designed to present a user-friendly fitness test protocol on the smartphone, including audiovisual cues and instructions, whilst simultaneously measuring and recording the test result data. In order to deliver the personalized exercise program via the smartphone, an assorted collection of exercises graded for different levels of movement abilities and specifically designed to meet motor fitness requirements for older adults, was developed, photographed, filmed, and uploaded to the new application.

We enrolled 52 volunteers in the pilot study. Based on remote smartphone assessment of their fitness level at baseline, participants were assigned a 6 week personalized exercise program. Each participant underwent the smartphone fitness assessment at baseline and again at 6 weeks after completion of the personalized exercise program. The results of remote smartphone fitness assessment were validated against “gold standard” fitness testing of the same components among the pilot study participants, who were also assessed at baseline and after 6 weeks in the study sports laboratory. The results of the pilot study provided proof of concept, with both improved fitness and good adherence confirming the benefits and feasibility of remote fitness assessment for guiding home personalized exercise programs among healthy adults aged > 65. Artificial intelligence (AI) was used to analyze data collected in the pilot study (from remote fitness testing before and after the different exercise components within the personal exercise plans) in order to further refine the study tool. As the study data base continues to enlarge, with subsequent big-data collection from additional participants, it is planned that AI will be integrated into the study tool to constantly refine and optimize the match between a participant’s fitness assessment and their most suitable personalized exercise program.

Having successfully completed the pilot study, we present the protocol for the next study stage, which plans to conduct a prospective randomized controlled trial using the study tool among healthy older people. Specifically, the study objectives are to investigate the effectiveness of a remotely delivered personalized 8-week multicomponent exercise program based upon remote individual fitness assessment, compared either to the updated WHO guidelines (active-control) or to no intervention (control). We hypothesize that participants in the personalized experimental group will show greatest motor improvement in balance, strength, and flexibility than participants with similar baseline fitness profiles in the active-control, with least changes observed among the control group.

## Methods/design

### Design and participants

The study is an interventional, prospective randomized control trial, comparing the study intervention to an active and passive control. Participants are healthy community dwelling volunteers aged ≥65 years, recruited using flyers and lectures by the study principal investigators at local elderly clubs, day centers, and independent living facilities. The study setting will be community based, either at home, local community centers or independent living facilities.

### Eligibility, inclusion and exclusion criteria

Healthy volunteers aged ≥65 years, males and females are eligible, who for inclusion must meet all the following criteria: 1) home or independent living; 2) fluent Hebrew speakers; 3) able to walk independently without help from another person; 4) functionally independent in dressing, toileting, grooming, washing, eating; 5) a smartphone user.

Exclusion criteria are ≥1 positive from the following: 1) Cognitive decline < 3/5 on Mini-Cog Score [18]; 2) Any hospitalization (> 24 h) or at least one Emergency Room referral in previous 12 months; due to unstable heart disease (congestive heart disease/rhythm disorder/ischemic heart disease/valvular heart disease) or neurological disease including balance or dizziness (cerebrovascular disease, vestibular disease, progressive neurological disease affecting gait or balance). (Information by self-report on direct questioning); 3) High risk of falling, as assessed by any positive answer to one of the 3 validated questions previously used in community-based exercise intervention and fall prevention studies [19]: a) Have you fallen over twice or more in the last year?; b) Have you fallen and hurt yourself in the last year?; c) Are you afraid that you might fall because of balance or walking problems?; 4) Unwilling to provide consent.

All participants will undergo assessment by the study physician in order to assess eligibility. The study physician will also gain informed signed consent, whereupon preliminary background data will be collected by trained research assistants. All participants who during the study trial experience an event listed in the exclusion criteria will be asked to discontinue the trial. Similarly, participants will be free to leave the trial at any time. In addition, participants will be asked to refrain from initiating new additional exercise programs during the study period.

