### Intervention

As shown in in the study flow chart (Fig. 1), the intervention will last 8 weeks. Following informed consent forms and collection of preliminary demographic and clinical data (T0), all participants will undergo fitness assessment by the test app before the intervention (T1), in which their fitness (Low or High) will be determined. They will then be re-assessed after 4 weeks (T2), after 8 weeks (T3), and after 12 weeks (follow-up T4). The testers will be well trained research assistants who will use their own mobile phone for the testing.

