### Intervention groups

***The experimental group (n = 100):*** participants will receive their personalized exercise program based upon the assessment of their performance level in each of the following fitness component: balance, flexibility, strength. Following the pilot study [17], and according to evidence supporting the advantages of exercising > 3 times/week [1], they will be instructed to exercise five times/week. Their videoed exercise program will be delivered to their personal mobile phone. An example of exercise as displayed on the mobile phone is presented in Fig. 2. The exercises are grouped into three target categories: 1) balance and lower body exercises, 2) upper body flexibility exercises, and 3) upper body strength exercises. Each exercise was coded according to target categories, and two levels of difficulty based on two levels of fitness: A (simple level) and B (advanced). Examples of typical exercises for each of the three motor components, for both levels of difficulty are demonstrated in our pilot study [17].
***An active control group (n = 100):*** participants will be asked, on individual basis, to exercise according to the official general guidelines published by the World Health Organization [1]. More specifically, they will be asked: 1) To perform leisure type aerobic exercise for 150-300 min or intensive exercise for 75-150 min. Per week. Examples such as walking, jogging, riding bicycle will be given; 2) In addition, they will be asked to perform ≥three times a week multicomponent physical activity that emphasizes functional balance and strength training at moderate or greater intensity. They will get the following examples of balance exercises: standing on toes, one leg-stance, walking while lifting knee, walking backwards, side walk while bending and extending knees. Examples of strength exercise: in standing position - lifting leg to side (abduction), extending straight leg backwards, lifting straight leg forward, sit and stand, standing against wall: pushing body with hands to wall, lifting arms to side – possibly with dumbbells.
***A control group (n = 100***): participants will be advised to continue their normal routine, and if interested, will be able use the smart app exercise program after the completion of the study.

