### Strategies to improve and monitor adherence

All participants from the experimental and active control groups will receive personal tutoring regarding his/her exercise program – personalized for the experimental group and general guidelines for the active control group. Participants in the experimental group will get specific guidance how to use their phone for watching their personalized program, and practice accordingly. In addition, they will get a small stand to place the phone in a viewable spot while exercising. Adherence to the programs will be monitored by a) Weekly phone calls to all participants. Participants in the experimental and active control groups will be inquired about difficulties or any comments they have regarding their exercise routine. In T2, T3 and T4 (every 4 weeks) they will be asked to report the average number of exercise sessions spent weekly in the previous 4 weeks. The passive control group will be informed in which week they are in the study, and when is the next fitness test due to occur.; b). The number of minutes spent using the study-app for exercising in the experimental group (the personalized exercise group) will be automatically recorded each time the smart-app exercise program is operated by participants in the intervention group.

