### Guidelines for safety

Participants in all groups will be instructed how to act in case of any medical problem arising during the study (see ‘Ethics approval and consent to participate’ in administrative information). Specifically, the experimental (personalized exercise) group will be asked to watch two films delivered to their mobile phone prior to starting the exercise program, participants (see [17]), which will include the following safety rules: “wear comfortable clothes”, “exercise bare foot or wear non-slip socks”, “find a quiet room at home with a place to put an exercise mattress, with an empty wall, and importantly – with a stable chair with back rest”, “don’t exercise if you have pains (greater than 3 on a 1-10 scale)”, “in knees and hands position you can put a mattress under your knees”, “block incoming calls to your phone while you use it for exercising”, “full safety comes first”, “if you feel unsafe, skip the exercise, or stop the training session” “stop if you feel dizzy”. In addition, since some exercises are performed on a mattress, a short film will be shown demonstrating how to get down and up from mattress. The active-control (general guidelines) group will be advised to wear comfortable clothes for exercising, to use comfortable tennis shoes for the aerobic exercise, and tennis shoes or bare foot for the strength and balance exercise, to take safety precautions for fall prevention, and to stop exercising if feels unsafe, or if has pain. Comprehensive insurance will cover the possibility of any medical complications incurred during the study, and the potential need for compensation.

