### Primary outcomes

The primary outcome measures are the changes in the following motor components, all of which are included in the remote fitness assessment (see Table 1 and Additional file 1): static balance (postural control in standing), dynamic balance (postural control while moving), strength (muscle endurance) of upper and lower extremities, and flexibility (range of motion in upper and lower body). All outcomes will be measured among all participants at baseline (T1), at 4 weeks (mid-intervention) (T2), at 8 weeks (end of intervention) (T3), at 12 weeks (one-month post intervention) (T4).

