#### Data analysis

The following 2-ways ANOVAs with repeated measures (3 treatment groups X 4 times measurements – T1-T4) will be conducted for each digital marker as follows:For all participantsSeparately for each of the following four subgroups: young women and young men (age 65-74), and old women and old men (age 75+).Separately for each of the two levels of fitness (Low and High) for each component. For example: low level of balance performance in the experimental group (personalized) compared to low level of balance in the control groups.Bonferroni will be used for post-hoc analyses, and False Discovery Rate [27] will be used to account for multiple comparisons.

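### A listed in-trial event takes the participant out of the trial, not only out of the exercise, so assessments after the event are lost for those who comply (minor, cheap to fix)

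*Protocol article*

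**What the plan says.** The rule is in the protocol article under Eligibility, inclusion and exclusion criteria: "All participants who during the study trial experience an event listed in the exclusion criteria will be asked to discontinue the trial". The next sentence treats voluntary withdrawal as the same kind of exit: "Similarly, participants will be free to leave the trial at any time".

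The exclusion list contains two or more falls in a year, a fall with injury, fear of falling, and hospital or Emergency Room care for unstable heart disease or for neurological disease including balance problems.

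The Intervention section schedules reassessment at 4, 8 and 12 weeks (T2, T3, T4). The passive control arm receives no exercise; under Intervention groups, "participants will be advised to continue their normal routine". On outcomes, the article states: "The primary outcome measures are the changes in the following motor components". These components are static and dynamic balance, strength and flexibility. Data analysis plans a repeated-measures ANOVA of three groups by four times, T1 included, for each digital marker. Mood and the Flanker task are also collected at T1 to T4 (Additional data).

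**The concern.** Stopping an exercise programme and stopping outcome measurement are separate decisions, and the rule merges them. Three features of the text point to leaving the study: the word used is trial, the adjoining sentence is about leaving the trial, and the rule binds passive controls, who have no study exercise to stop.

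The triggering events happen after randomization, and exercise may cause or prevent them. They bear on the balance and leg-strength outcomes, and less on arm and torso flexibility. Those who leave may therefore have changed differently from those who stay, and their number may differ by arm. An analysis plan can make assumptions about the missing visits, but it cannot supply them.

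**Working it through.** **1. The article's own figure.** The article states 86% power at f = 0.15 with 100 per arm. For the between-groups factor, lambda = N f² m / (1 + (m - 1) rho), with N = 300, m = 4 and df 2 and 297. Alpha 0.05 and rho 0.5 are assumed, since neither is stated. Then lambda = 300 × 0.0225 × 4 / 2.5 = 10.8 and power is 0.842; rho = 0.45 gives 0.865. The stated figure is reproduced. With assumed losses of 5%, 10% and 20% in a complete-case analysis, power at f = 0.15 is 0.822, 0.799 and 0.747, and at f = 0.25 it is still 0.995 at 20% loss. For the group-by-time interaction, the term that tests change, power at f = 0.15 and 20% loss is 0.9998. Power is not the main issue.

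**2. Bias formula.** Let p be the share of an arm removed and d how much worse the leavers' change is than the stayers'. If the stayers' mean change is S, the whole arm's mean is S - p d, so restricting to stayers flatters the arm by p d. Between two arms:

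bias = p1 d1 - p2 d2.

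A gap between stayers and leavers that is already present at T1 and persists unchanged gives d = 0 for change, and so no bias in change. With 10% against 3% removed and a 1 SD gap, a comparison at follow-up alone would be off by (0.10 - 0.03) × 1 = 0.070 SD, but the comparison of change by 0. Only event-related decline or a differing response matters.

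**3. Assumed scenarios** (exercise arm against passive control, equal d; the article gives no rates):

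| Removed, exercise / passive | d (SD) | Bias (SD) |
|---|---|---|
| 5% / 2% | 0.25 | 0.03 × 0.25 = 0.0075 |
| 5% / 2% | 0.5 | 0.03 × 0.5 = 0.015 |
| 10% / 3% | 0.5 | 0.07 × 0.5 = 0.035 |
| 2% / 5% | 0.25 | -0.03 × 0.25 = -0.0075 |
| 2% / 5% | 0.5 | -0.03 × 0.5 = -0.015 |
| 5% / 10% | 0.5 | -0.05 × 0.5 = -0.025 |
| equal rates | equal | 0 |

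**4. Scale.** The standard error of a two-arm difference in change is sqrt(2/100) × sqrt(2(1 - r)), where r is the correlation of T1 with follow-up: 0.141 SD at r = 0.5 and 0.110 SD at r = 0.7. The largest scenario is 0.035/0.141 = 25% of it, or 0.035/0.110 = 32%. With equally spaced means, f = 0.15 implies a personalized-against-passive difference of 2 × 0.15 / sqrt(2/3) = 0.367 SD, and 0.035/0.367 = 10%.

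**5. What continued assessment would keep.** Table 1 lists 10 tests, four of them balance tests. If all four are withheld, 10 - 4 = 6 remain. The analysis unit is the marker, however, and there are 42. From Table 1, sit-to-stand gives 2, three flexibility tests on two sides give 6, and two arm-strength tests on two sides give 4, in total 12. The other 42 - 12 = 30 fit the balance tests: one-leg and tandem stance on two sides plus two walks are 6 performances, at 5 markers each. Additional file 1 is not shown, so this split is inferred. On it, 12/42 = 29% of markers are kept.

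**The case against.** The best defence is safety. The fitness tests, which include one-leg stance and backward tandem walking, are the passive arm's main study exposure. Ending participation for someone who no longer meets the entry criteria is a defensible choice. This stands as a reason to withhold tests judged unsafe, but not as a reason to stop every assessment: mood and the Flanker task are not physical performance tests.

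The Primary outcomes section says that all participants are measured at every time point. This leaves some room for continued follow-up, as might the full protocol, which is not shown. But it is a general schedule with no provision for people asked to leave, and it does not override the specific rule. If continued measurement is intended, the sentence still needs rewording.

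The fix also recovers least where bias is most plausible. Five of the six non-balance tests are upper-body, and sit-to-stand or weighted arm lifts may be withheld after a cardiac event. This stands in full and limits the benefit.

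A reader might infer more than the article supports:

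- **A large bias, or one that favours a particular arm.** No event rates are given, and participants are screened for low fall risk and followed for 12 weeks.
- **Events detected unequally by arm.** The article provides for "Weekly phone calls to all participants", and "Participants in all groups will be instructed how to act in case of any medical problem arising during the study".
- **Loss of all of T2 to T4 for everyone with an event.** Participants are only asked to stop, and visits before the event are kept.
- **Fear of falling as a trigger.** It is a screening answer, and no repeat of the question is described.

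**Conclusion.** The point holds as a minor one. As written, the rule ends outcome collection after a post-randomization event related to some of the primary outcomes, for those who comply. The bias in a difference in change is about -0.025 to +0.035 SD across the scenarios tried, with zero possible and the direction unknown. The top of that range needs 10% against 3% removed within 12 weeks and leavers who do 0.5 SD worse; all of these rates and declines are assumptions. The reason to act is that the lost measurements cannot be recovered and the change is cheap, not that a material distortion is expected.

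**What to change.** Reword the rule so that a listed event stops the study exercise where the study physician so judges, while consenting participants stay in the remaining scheduled T2-T4 assessments, including mood and the Flanker task. Omit any fitness test the physician judges unsafe and record the reason. Analyse the data in the randomized arm, and report listed events and discontinuations by arm. The right to leave at any time is unchanged.

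The cost is one reworded rule and a few retained visits. Balance markers may still be missing, so at most 6 of 10 tests (about 12 of 42 markers) are kept if all balance tests are withheld, and fewer after a cardiac event. Asking all three arms the same question on falls, emergency visits and admissions in the existing weekly calls is an optional extra.
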